## Methods/Design

### Ethical and governance approval

Approval was granted by the Central Committee on Research involving Human Subjects (in Dutch Centrale Commissie Mensgebonden Onderzoek (CCMO)), Ref: NL.24770.041.08.

### Study design

CHO-CAP consists of a baseline cohort and a nested matched-cohort study, both executed in parallel to the CAPiTA trial.

#### Baseline cohort

The study population included in the CAPiTA trial consists of 84,496 community-dwelling persons 65 years and older randomized to receive 13vPnC or placebo (for details of inclusion and exclusion criteria see Hak et al. [1]). All patients included were eligible to participate in the CHO-CAP study. For the baseline cohort, CAPiTA participants were approached at the vaccination centre for participation in CHO-CAP. After inclusion in the CAPiTA study and receipt of study vaccination, participants received written information on the CHO-CAP study. Subjects were asked to fill in a questionnaire and to return it, together with a signed informed consent form, in a pre-stamped envelope. Those who did form the source population (i.e. baseline CHO-CAP cohort) are eligible for participation in the nested matched cohort study (see Figure 1). Subjects returning their questionnaire without informed consent form were contacted a second time with the request to also return a signed informed consent.

**Figure 1 F1:**
[figure not shown]
Flow chart of the CHO-CAP study with different (sub-)cohorts and anticipated number of participants.

#### Nested matched cohort study

As part of the CAPiTA trial, patients with a clinical suspicion of CAP are tracked in 56 Dutch sentinel hospitals. The duration of follow-up within CAPiTA is defined by the number of primary endpoints captured (i.e. 130 first CAP episodes caused by vaccine-type *S. pneumoniae* serotypes). It is expected that around 2,000 CAP episodes will occur within the study population [1]. Assuming a response rate of ~30%^a^ for the baseline questionnaire, we expected approximately 600 first CAP episodes among CHO-CAP participants. Local research nurses in sentinel hospitals notify the CHO-CAP team of newly admitted CAPiTA patients with a clinical suspicion of CAP directly after hospital admission and at the time of discharge. After discharge, eligible patients (i.e. CHO-CAP participants) will be asked to participate in the prospective cohort study for a period of one year. Patients are informed (orally and by written information) that participation involves one interview during a home visit, with three subsequent questionnaires to be completed during the 12 month period. Patients again provide informed consent upon inclusion in the prospective cohort study. Exclusion criteria for the prospective cohort study are hospitalization for a second (or further) hospitalization for CAP related complaints, inability to complete questionnaires, or a recent diagnosis of malignancy as the study was considered too burdensome for this latter group.

For each patient with CAP in the prospective cohort study (“diseased” cohort), two matched unaffected subjects (i.e. no CAP episode until the time of matching) will be selected from the baseline population for inclusion in the “non-diseased” cohort (see Figure 1). Matching is based on age (same age, with allowance of 3 years age difference), gender and baseline health status (same EQ-5D score [22], with maximum allowance of 5 percent points difference). Expectations are that both in the short-term and the medium term, CAP patients consume more medical resources, require more (in)formal help, might experience more trouble to get back to their daily activities, and have a lower quality-of-life than their non-diseased peers. Furthermore, mortality, both within-hospital as during the 12 months follow-up period, is expected to be higher in CAP patients than in controls.

The inclusion of two unaffected controls increases the validity of study results and diminishes the risks from loss to follow-up. Exclusion criteria for controls are admission to hospital for a CAP episode since vaccination, inability to complete questionnaires, or having a recently diagnosed malignancy, as the study was considered too burdensome for the latter group. Controls also provide informed consent at start of follow-up.

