**Methods/Design:**

CAPiTA is a placebo-controlled double-blind RCT evaluating the effectiveness of a 13-valent conjugated pneumococcal vaccine in preventing vaccine-type pneumococcal CAP in 84,496 elderly in the Netherlands. Participants of CAPiTA, who consented and provided information on health status (EQ-5D) and socio-demographic background at the time of vaccination, constitute the source population of CHO-CAP and are eligible for the nested matched cohort study. CHO-CAP patients hospitalized with CAP form the “diseased” cohort and the “non-diseased” cohort consists of unaffected persons (i.e. no CAP). Observations in the diseased cohort and in matched controls from the non-diseased cohort are used to determine excess costs and QoL changes attributable to CAP.

Based on an estimated 2,000 CAPiTA participants being hospitalized with CAP and an assumed CHO-CAP participation rate of 30% of all CAPiTA participants (±25,000), 600 CAP episodes are expected among CHO-CAP participants (the “diseased” cohort). For each patient with CAP, two non-diseased CHO-CAP subjects will be selected from the CHO-CAP cohort, with matching for age, gender and EQ-5D baseline-score. Data on healthcare and non-healthcare resources use, quality-of-life (using EQ-5D and SF-36 questionnaires) and selected health outcomes will be collected at 0, 1, 6 and 12 months after hospitalization for CAP.

The CHO-CAP study was approved by the Central Committee on Research involving Human Subjects in the Netherlands.

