#### Nested matched cohort study

Each identified CHO-CAP participant hospitalized with CAP and interested in participation in the prospective “diseased” cohort is visited at home by a trained interviewer. Informed consent is obtained during this home visit. If consent is given, questions on health status, co-morbidities, current living situation and healthcare resources used before hospital admission are collected (see details in Table 2). A diary for own recording of healthcare resource use and other out-of-pocket expenses in the forthcoming period (i.e. one month) is explained and provided. Healthcare resources used during hospital admission (i.e. length of hospitalization, medication, diagnostics, interventions (e.g. surgery), complications, ICU admission) is collected from hospital databases by local trial nurses.

**Table 2 T2:** **Data collection in matched cohort-study**^
**a**
^

**Cohort**	**Diseased cohort (i.e. CAP patients)**** *During home visit; Contact at baseline* **	**Non-diseased cohort (i.e. unaffected (no CAP) persons)**** *During home visit; Contact at baseline* **	**Diseased/non-diseased cohort**** *Per post; Contact at 1, 6 and 12 months* **

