## Discussion

The infrastructure of the CAPiTA trial offers a unique opportunity for prospective collection of health outcomes, QoL and cost data of patients hospitalized with CAP. Such data will facilitate the construction and validation of health economic models on cost-effectiveness and cost-utility of 13vPnC in the future, should this become necessary if vaccine efficacy and safety is demonstrated.

One of the limitations of the current study is that we might mainly reach the ‘healthier’ part of the community-dwelling CAPiTA participants, as older and more diseased subjects may be less willing to participate in additional research projects next to the main CAPITA trial. To gain insight into this possible bias, we will compare the baseline demographic data of the CHO-CAP cohort population with the larger CAPiTA population. Further, data gathered within the CAPiTA-study will enable us to compare CAP cases from the current CHO-CAP cohort with all CAP cases, for instance with regard to duration of hospitalization and occurrence of complications.

With an expected 600 CAP episodes we expect to constitute one of the biggest prospectively studied cohorts of hospitalized elderly with CAP with regard to resources use and QoL data. Strengths of this study further include collection of out-of-pocket costs of patients and productivity losses of both patients and their caregivers and the follow-up period of up to one year post-discharge. Our study is expected to add more in-depth knowledge on the short and longer term outcomes of pneumonia in elderly.

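### The matched comparison covers only CAP patients discharged alive and able to respond, yet it is presented as the burden attributable to hospitalized CAP

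*Protocol article*

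**What the plan says.** Study design, Nested matched cohort study: research nurses notify the CHO-CAP team of suspected CAP at admission and again at discharge, but the invitation comes later: "After discharge, eligible patients (i.e. CHO-CAP participants) will be asked to participate in the prospective cohort study for a period of one year". Besides a second or further CAP admission, the exclusions are "inability to complete questionnaires, or a recent diagnosis of malignancy as the study was considered too burdensome for this latter group". Two controls are then selected for each CAP patient already in the prospective cohort. Their exclusions are similar: "Exclusion criteria for controls are admission to hospital for a CAP episode since vaccination, inability to complete questionnaires, or having a recently diagnosed malignancy".

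Data collection, Nested matched cohort study: an interviewer visits the patient at home, and "Informed consent is obtained during this home visit". The 1-, 6- and 12-month contacts are counted from that visit.

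Abstract, Methods/Design: observations in the two cohorts "are used to determine excess costs and QoL changes attributable to CAP". The diseased cohort is described there simply as CHO-CAP patients hospitalized with CAP.

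Study design, Nested matched cohort study, also states an expectation: "mortality, both within-hospital as during the 12 months follow-up period, is expected to be higher in CAP patients than in controls".

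Statistical analysis makes the comparison of the matched cohorts the main analysis. The Discussion acknowledges that healthier people may be over-represented, attributes this to willingness to take part, and says CAPiTA data will make it possible to "compare CAP cases from the current CHO-CAP cohort with all CAP cases", giving length of stay and complications as examples.

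**The concern.** Surviving the admission, surviving until the home visit and being able to fill in a questionnaire all come after CAP and can be changed by it. Entry to the diseased cohort is therefore conditional on part of the outcome. Controls face the same inability criterion, but without a recent CAP admission that could have caused the inability, so the criterion is not neutral between cohorts. Matching on age, gender and EQ-5D at vaccination cannot repair selection that happens after the exposure.

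Both primary objectives, the 12-month differences in quality of life and in resource use, rest on this comparison. Without qualification, a figure for patients who came through CAP well enough to respond may be read, or used in a health-economic model, as the figure for a CAP hospitalization. The expected within-hospital mortality difference cannot appear in the enrolled cohort, which contains no index in-hospital deaths by construction.

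**Working it through.** **The plan's own figures.** 2,000 × 0.30 = 600 CAP episodes, and 600 × 2 = 1,200 controls. Both reproduce. The 600 counts episodes before any loss to death, inability, malignancy or refusal, and Sample size treats it as a maximum. If 5-15% die in hospital and 0-10% of survivors are unable to respond (both assumed), the ceiling falls to between 600 × 0.95 = 570 and 600 × 0.85 × 0.90 = 459.

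**Who can enter the matched comparison.**

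| Baseline CHO-CAP member with a first CAP admission | Can enter? | Reason |
|---|---|---|
| Dies in hospital | No | Asked only after discharge |
| Dies between discharge and home visit | No | Consent is given at the visit |
| Survives, unable to complete questionnaires | No | Exclusion criterion |
| Survives, able, consents, then dies | Yes | Death falls within follow-up |

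An excluded case forms no matched set, because controls are chosen for enrolled patients only.

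**QoL illustration.** The article gives no mortality rate, utility or QALY loss, so every input is an assumption: in-hospital mortality m = 5-15%; mean control utility 0.85 over 12 months; 12-month loss in enrolled survivors L = 0.05-0.12 QALY; death at day 0, valued at 0; no control mortality.

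Loss per hospitalized case = (1 − m) × L + m × 0.85. Understatement = 1 − L / (loss per hospitalized case).

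| L | m = 5% | m = 10% | m = 15% |
|---|---|---|---|
| 0.05 | 0.0900 (44%) | 0.1300 (62%) | 0.1700 (71%) |
| 0.08 | 0.1185 (32%) | 0.1570 (49%) | 0.1955 (59%) |
| 0.12 | 0.1565 (23%) | 0.1930 (38%) | 0.2295 (48%) |

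For example, at L = 0.08 and m = 10%: 0.90 × 0.08 + 0.10 × 0.85 = 0.157, and 1 − 0.08/0.157 = 49%. The sign does not depend on the exact inputs: the understatement is positive whenever the survivor loss is smaller than the loss from death.

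A second set of assumptions (control utility 0.75-0.85, L = 0.05-0.10, same m) has enrolled survivors showing 29-75% of the loss per case. If 10% of survivors are also excluded as unable, with an assumed loss of 0.30, that share falls to 26-66%.

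**Cost illustration.** Let r be the excess cost of a fatal case divided by that of an enrolled survivor. Full cost / observed cost = (1 − m) + m × r. At m = 15%, r = 0.25 gives 0.85 + 0.0375 = 0.89, and r = 3 gives 0.85 + 0.45 = 1.30. The ratio falls on either side of 1.

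**The case against.** The strongest reply is that CHO-CAP is meant as a post-discharge study. Background says CAPiTA covers the hospitalization period and that effects extend beyond it, and the Discussion describes follow-up of up to a year after discharge. No QALY endpoint with death scored 0 is defined, and the Discussion offers the data only as help towards possible future models. Such a model could take survivor utility and in-hospital mortality as separate inputs. This stands in part: a survivor comparison is a legitimate quantity. It does not rescue the unqualified claim in the abstract, and no section commits to combining the two sources. Nor would adding in-hospital mortality restore survivors excluded as unable.

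It can also be said that handling of deaths belongs in an analysis plan not shown here. That is fair for analysis detail. Eligibility, point of entry and what the comparison is said to measure are fixed in this article.

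Some stronger readings are tempting but unsupported:

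- A reader might infer that in-hospital mortality cannot be observed at all. Nurses report at admission and at discharge, and the baseline database is updated for deaths, so it is potentially observable among baseline CHO-CAP members. Only a contrast within the enrolled cohort is impossible, and the mortality sentence states an expectation, not a listed objective.
- A reader might infer that only well survivors are enrolled. Table 2 anticipates discharge to a nursing home, and non-responders are phoned.
- A reader might infer that costs are understated because expensive fatal stays are missing. Death also ends later costs, so the sign is open.

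**Conclusion.** The concern holds as a mismatch between the population compared and the claim made for it. The main comparison estimates burden among consenting CAP patients who left hospital alive and could respond; it does not estimate the burden of a CAP hospitalization. With death valued at 0, the QoL loss is understated. The 23-71% range should not be read as a measured bias: it rests wholly on assumed rates, and it charges each in-hospital death a full year at 0.85 with no control mortality, which is near the most such deaths could add. Incapacitated survivors, left out of that range, would add to it. The cost bias has no determinable direction (full/observed 0.89-1.30 under the assumptions shown). The Discussion's comparison with all CAP cases would describe selection but corrects nothing, and in-hospital death is not among its examples. Confidence is high on the selection and low on its size. This should be fixed. It does not invalidate the study, because the survivor result remains usable once labelled.

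**What to change.** 1. In the abstract's Methods/Design, in Objective and in Statistical analysis, state that the matched comparison estimates burden among consenting patients discharged alive and able to respond. Do not claim a within-hospital mortality contrast from that cohort.
2. Add an analysis starting at the admission date, of all baseline CHO-CAP members with a first CAP hospitalization. Take vital status from the nurse notifications and database updates, and set utility to 0 from death. Select controls on file, by the existing matching variables and from the same index date, with their own vital status. Use length of stay and complications from CAPiTA. Use ICU and cost data for non-enrolled patients only where they are held and covered by the baseline consent; the article does not show that they are held.
3. Extend the Discussion's comparison of enrolled cases with all CAP cases to include in-hospital death.

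Cost: wording, data linkage and one further analysis, with no additional visits or patients. The downside is that QoL and later costs of excluded survivors have to be modelled, with a sensitivity range reported, and that use of non-enrolled patients' data must first be checked against the baseline consent.

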### Data collection

#### Baseline CHO-CAP cohort study at time of vaccination

At the time of vaccination subjects were asked to provide information on:

•health status (5 item EQ-5D instrument [22] (see Table 1)),

•socio-demographic status (i.e. education and current living situation)

•self-reporting of previous manifestations of stroke or other cardiovascular disease events.

**Table 1 T1:** **The 5-item EQ-5D questionnaire (Source:**[22]**)**

**Mobility**	
I have no problems in walking about	□
I have some problems in walking about	□
I am confined to bed	□
**Self-care**	
I have no problems with self-care	□
I have some problems washing or dressing myself	□
I am unable to wash or dress myself	□
**Usual activities (e.g. work, study, housework, family or leisure activities)**	
I have no problems with performing my usual activities	□
I have some problems with performing my usual activities	□
I am unable to perform my usual activities	□
**Pain/discomfort**	
I have no pain or discomfort	□
I have moderate pain or discomfort	□
I have extreme pain or discomfort	□
**Anxiety/depression**	
I am not anxious or depressed	□
I am moderately anxious or depressed	□
I am extremely anxious or depressed	□

After receipt of the completed baseline questionnaire, CAPiTA participant ID, informed consent, socio-demographic data, and EQ-5D index value for health status (see below) were registered in the CHO-CAP database, with linkage to the CAPiTA database for age, gender and place of residence/region. Regular updates to adjust for changes in place of residence or to include loss-to-follow up (e.g., due to death), take place.

Following the standards set up by the Euroqol organisation, the developers and owners of the EQ-5D instrument [22], the 5-items from the EQ-5D questionnaire were transferred into a single value between 0 (worst imaginable health status) and 1 (best imaginable health status) [23].

#### Nested matched cohort study

Each identified CHO-CAP participant hospitalized with CAP and interested in participation in the prospective “diseased” cohort is visited at home by a trained interviewer. Informed consent is obtained during this home visit. If consent is given, questions on health status, co-morbidities, current living situation and healthcare resources used before hospital admission are collected (see details in Table 2). A diary for own recording of healthcare resource use and other out-of-pocket expenses in the forthcoming period (i.e. one month) is explained and provided. Healthcare resources used during hospital admission (i.e. length of hospitalization, medication, diagnostics, interventions (e.g. surgery), complications, ICU admission) is collected from hospital databases by local trial nurses.

**Table 2 T2:** **Data collection in matched cohort-study**^
**a**
^

**Cohort**	**Diseased cohort (i.e. CAP patients)**** *During home visit; Contact at baseline* **	**Non-diseased cohort (i.e. unaffected (no CAP) persons)**** *During home visit; Contact at baseline* **	**Diseased/non-diseased cohort**** *Per post; Contact at 1, 6 and 12 months* **
**Data collected:**			
*Demographic data*	➣ Current living situation	➣ Current living situation	➣ Current living situation
*Quality-of-life data*			
➣ 5-item EQ-5D instrument & VAS [22]	➣ As on day of interview	As on day of interview	As on day of interview
	➣ Referring back to worst moment of CAP episode		
	➣ Referring back to time previous to CAP episode		
➣ 36-item SF-36D instrument [24,25]	n.a.^b^	➣ 36-item SF-36D instrument [24,25]	➣ 36-item SF-36D instrument[24,25]
*Co-morbidities*			
➣ Stroke and/or cardio-vascular event	➣ Since participating in CAPiTA;	➣ Since participating in CAPiTA,	➣ Since last contact moment;
➣ 28-item standard list of major comorbid diseases developed by Statistics Netherlands	➣ 28-item standard list of major comorbid diseases	➣ 28-item standard list of major comorbid diseases	n.a.^b^
*Medical resources used:*			
➣ Medication used	➣ Previous to hospital admission to treat CAP;	n.a.^b^	➣ Since last contact moment;
➣ GP; emergency department and other medical specialist consultations (phone; office and home consultation(s))	➣ Previous to hospital admission to treat CAP;	n.a.^b^	➣ Since last contact moment;
➣ Outpatient visit(s) and treatment(s)	n.a.^b^	n.a.^b^	➣ Since last contact moment;
➣ Hospital admission(s) and treatment(s)	n.a.^b^	n.a.^b^	➣ Since last contact moment;
➣ Institutional care admission(s) others than hospital	n.a.^b^	n.a.^b^	➣ Since last contact moment;
*Home care*			
➣ Professional home care used	➣ Previous to hospital admission during the CAP episode?	In month previous to interview	➣ Since last contact moment;
*Productivity losses due to absence from patient/control from unpaid work (including replacement)*			
➣ Is unpaid work conducted on a regular base.	➣ Previous to CAP hospital admission	n.a.^b^	➣ Since last contact moment;
➣ Absent from unpaid work: For how long. Who took the work over?	➣ Previous to hospital admission during the CAP episode?	n.a.^b^	➣ Since last contact moment;
*Productivity losses due to absence of caregiver(s) from (un)paid work*			
➣ Informal home care used: By who? And for how long?	➣ Previous to hospital admission during the CAP episode	n.a.^b^	Since last contact moment;
*Travel costs:*			
Method of transport and cost	➣ To hospital when admitted with CAP	n.a.^b^	n.a.^b^
	➣ After discharge from hospital to home/nursing home	n.a.^b^	n.a.^b^
*Other cost/out-of-pocket expenses* (open question)	n.a.^b^	n.a.^b^	➣ Since last contact moment;

Note:

a) Questionnaires (in Dutch) are available on request from first author.

b) n.a. = not applied.

Similar procedures are followed for the controls. An identified and eligible control who expressed interest to participate at the time of vaccination is visited at home. If consent is given, a questionnaire similar to that administered in the “diseased” cohort is provided (see details in Table 2).

In both the “diseased” and “non-diseased” cohorts, further data is collected on 1, 6 and 12 months after the initial home visit. Questionnaires are send by post, with the request to fill-in and send back within a week. If no response is received, participants are contacted by phone. This follow-up questionnaire addresses current living conditions, quality-of-life, co-morbidities and healthcare resources used (Table 2). A new diary for recording of healthcare use and other out-of-pocket expenses in the forthcoming period is provided once the questionnaire has been returned.

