### Objective

CHO-CAP comprises the collection of cost data and quality-of-life data in elderly with and without CAP. The primary objectives are:

1. To determine, during a 12 month follow-up period, differences in quality-of-life of elderly with and without CAP.

2. To determine, during a 12 month follow-up period, differences in resource use (healthcare and non-healthcare) in elderly with and without CAP.

The secondary objective is to describe the baseline health status and quality-of-life of a community-dwelling elderly population eligible for participation in the CAPiTA study.

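### From hospital admission to the home visit, no recall window in Table 2 covers CAP cases' unpaid-work absence, caregiver absence or out-of-pocket expenses

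*Protocol article*

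**What the plan says.** The second primary objective (Objective section) is "To determine, during a 12 month follow-up period, differences in resource use (healthcare and non-healthcare) in elderly with and without CAP". The Discussion, like the Abstract, counts the non-healthcare items among the study's merits: "Strengths of this study further include collection of out-of-pocket costs of patients and productivity losses of both patients and their caregivers".

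The collection windows for cases are set in Data collection, Nested matched cohort study, and in Table 2:

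- **Recruitment:** "After discharge, eligible patients (i.e. CHO-CAP participants) will be asked to participate in the prospective cohort study". The home visit therefore follows the whole index stay.
- **Home visit, unpaid-work absence and who took the work over; informal care and caregiver absence:** asked for the time "Previous to hospital admission during the CAP episode".
- **Home visit, "Other cost/out-of-pocket expenses":** marked n.a., which the table note defines as not applied.
- **Home visit, travel:** the patient's transport to hospital and after discharge is asked.
- **Posted forms at 1, 6 and 12 months, counted from the home visit:** "Since last contact moment".
- **Diary:** handed over at the home visit, for the coming month.
- **The stay itself:** hospital databases, with this list: "Healthcare resources used during hospital admission (i.e. length of hospitalization, medication, diagnostics, interventions (e.g. surgery), complications, ICU admission").

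**The concern.** The index admission is the part of the episode in which a patient who does regular unpaid work cannot do it, and in which relatives are likely to miss work or incur expenses. The article names a source for the healthcare side of that period but none for the non-healthcare side.

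If the windows are applied as written, the case totals omit these items at the time when loss attributable to CAP is likely to be most concentrated. Controls have no index stay, so the omission has no counterpart on their side. A larger cohort would not remove the resulting bias, and an analysis plan cannot recover answers that were never asked for.

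**Working it through.** There is no stated figure to reproduce. The check is to place each window on one timeline for a case and see which segments are covered.

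| Item (cases) | Onset to admission | Admission to discharge | Discharge to home visit | After home visit |
|---|---|---|---|---|
| Unpaid-work absence, replacement | home visit | none | none | posted forms |
| Informal care, caregiver absence | home visit | none | none | posted forms |
| Out-of-pocket expenses | none | none | none | posted forms, diary |
| Patient's own transport | trip to hospital | – | trip after discharge | n.a. |
| Medication; GP, emergency and specialist consultations | home visit | hospital databases (in-hospital care) | none | posted forms |
| Outpatient visits | none | – | none | posted forms |
| Professional home care | home visit | – | none | posted forms |

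Three steps follow.

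1. **The first posted form cannot reach back into the stay.** Its window opens at the last contact. Table 2 treats the home visit as the baseline contact, and that visit comes after discharge.
2. **The uncovered stretch is longer than the stay.** For the first three rows it runs from admission to the home visit. For out-of-pocket expenses it starts at onset. The medication, consultation, outpatient and professional home-care rows share the gap from discharge to the visit.
3. **Length of the gap.** Gap = length of stay + days from discharge to home visit. The article gives neither. Assuming a total of 5 to 30 days, the gap equals 5/365 = 1.4% to 30/365 = 8.2% of a year. This is a share of time, not of cost, and it cannot be converted into cost from the documents.

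**What planned data can recover.** Table 2 asks whether unpaid work was done regularly before admission, and the hospital databases give length of hospitalization. Together they yield days of absence in hospital for patients with regular unpaid work. They do not yield who took the work over, caregivers' absence from work, or expenses.

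**The case against.** The strongest points on the other side, and what stands of each:

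- **Unpaid-work absence in hospital can be derived.** This stands. A reader might infer that the case total must contain no non-healthcare cost at all for the hospital days. The documents do not support that: the patient's transport is collected, and in-hospital absence follows from length of stay plus the regular-work item. The article does not state such a rule, however, and the rule leaves replacement, caregiver absence, expenses and the days after discharge uncovered.
- **The caregiver row asks about informal home care, which is largely nil while the patient is in hospital.** This stands for the stay, and home care that the patient normally receives may even fall. What is missed is caregivers' absence from work around the admission and, after discharge, home care itself.
- **Every case affected, with a large total of lost hours.** A reader might multiply days, caregiver hours and 600 cases. Days and hours would be pure assumption, 600 is given under Sample size as an upper limit, and not every case does unpaid work or has a caregiver. No such total is supported.
- **Controls also lack pre-visit data on these items.** This is correct, because Table 2 marks them n.a. But controls have no index episode before their visit, so they lose no CAP-attributable use.
- **Follow-up may start only after hospitalization.** The article describes 12 months after hospitalization (Background) and up to one year after discharge (Discussion). Yet in-hospital healthcare use is collected, so the stay is part of the costing. Even if follow-up is counted from discharge, the days up to the visit fall inside it and are uncovered.
- **Table 2 condenses Dutch questionnaires that are not shown.** The phrase on the episode could be short for before admission or during the episode. The wording would then still need correcting, and out-of-pocket expenses would still be marked as not asked.

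**Conclusion.** The gap holds as a feature of Table 2 as written. Between admission and the home visit, no instrument records cases' unpaid-work absence and replacement, informal care and caregiver absence, or out-of-pocket expenses. Only the patient's own transport is collected.

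The excess non-healthcare cost under the second primary objective is probably biased downward. The direction is probable rather than certain, because informal home care may drop during a stay. The size cannot be given from the documents.

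The conclusion assumes that the questionnaires follow the windows in Table 2 and that no unpaid-work absence is imputed for hospital days. With such imputation the bias shrinks for that item but remains for the others. The change is worth making because it is cheap and because the article presents these very items as a strength.

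**What to change.** - **Home visit, cases, non-healthcare items.** In Table 2, set the window for unpaid-work absence and replacement, and for informal care and caregiver absence, to *from onset of the CAP episode up to the home visit*. Ask out-of-pocket expenses for the same window. Stopping at discharge would leave the days up to the visit uncovered.
- **Home visit, cases, healthcare items.** Apply the same end point to post-discharge medication, GP and outpatient care, and professional home care.
- **Cases already interviewed.** For those reporting regular unpaid work, derive absence in hospital from length of stay. State that this counts hospital days, not working days. Report that caregiver-absence and out-of-pocket totals exclude the period from admission to home visit, and qualify the claimed strength accordingly.

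The cost is a rewording of a few items in an existing interview and one derivation rule. Recall becomes slightly longer, and earlier cases carry a derived value in place of a reported one. Because controls have no pre-visit data on these items, the added segment should be shown separately, so that readers can see that it includes some background use.
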